2.7 Data collection and management

The demographic and baseline characteristic data will be collected by screeners when the participants are recruited. Research assistants will conduct quality control of data collection and be responsible for data entry. The project manager will be responsible for initial data cleaning, identifying, coding, and converting into the proper format for data analysis.

2.8 Statistical analysis

Baseline characteristics and outcomes between groups will compare using the t-test or non-parametric test for continuous variables and Pearson chi-squared or Fisher’s exact test for categorical variables. Subgroup analysis stratified by participants’ sex will be used for the primary outcomes.

All data will be analyzed with SPSS 21.0 (IBM, Chicago, IL, USA) software packages. The statistical significance is defined as two-sided P value of <0.05.

Participants recruitment

Eligible participants n=222

Baseline assessment

Exclusion (reasons): n=

Not meeting inclusion criteria: n=

Declined to participate: n=

Other reasons: n=

Randomization allocation

Baduanjin training group

n=111

Control group

n=111

Drop out (reasons): n=

Intervention group: n=

Control group: n=

Outcomes assessment after intervention: lumbar muscle strength, lumbar proprioception function, self-reported symptom intensity, stress, self-efficacy, attention, cardiopulmonary function, flexibility, hand grip strength, self-esteem, mood and mindfulness, quality of life, quality of sleep and adverse events

Follow up for 12 weeks

Lost to follow up: n=

Intervention group: n=

Control group: n=

Above outcomes assessment after follow-up period

Included analysis: n=

Intervention group: n=

Control group: n=

Statistic analysis

Excluded from analysis: n=

Intervention group: n=

Control group: n=

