2.1 Sample size

We use the improvement of lumbar flexion muscle strength as the main effect indicators to estimate the sample size, and our preliminary test data from 20 eligible participants indicated the means with standard deviation of the lumbar flexion muscle strength was 258.25 newton (N) and 114.19 N respectively. To detect a 20% mean difference on the Baduanjin exercise at the end of intervention, 101 participants per group are calculated according to the formula with a type I error of 5% (α= 0.05) and 90% power (β= 0.10). Assuming a dropout rate of 10% for follow-up, the sample size is 111 for each group.

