2.6 Outcome assessment

All primary and secondary outcomes will be assessed at baseline, 13 weeks (end of intervention), and 25 weeks (after the 12-week follow-up period).

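### Section 2.8 compares continuous outcomes without baseline adjustment although every primary and secondary outcome is measured at baseline; adjusting would gain precision at no cost

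*Protocol*

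**What the plan says.** Section 2.8 covers baseline characteristics and outcomes in a single sentence: "Baseline characteristics and outcomes between groups will compare using the t-test or non-parametric test for continuous variables". It mentions no covariate, regression model or change score. The only further analysis it describes is a subgroup analysis by sex for the primary outcomes.

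Section 2.6 says that "All primary and secondary outcomes will be assessed at baseline", and again at weeks 13 and 25.

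Section 2.1 begins "We use the improvement of lumbar flexion muscle strength as the main effect indicators to estimate the sample size". The figures it then uses describe the strength level and not a change: "the means with standard deviation of the lumbar flexion muscle strength was 258.25 newton (N) and 114.19 N respectively", from 20 participants. The target is given as "To detect a 20% mean difference on the Baduanjin exercise at the end of intervention".

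Section 2.3 sets 1:1 allocation and mentions no stratification.

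**The concern.** The baseline value of each outcome will be in hand, but the stated analysis does not use it in estimating the effect. Lumbar flexion strength varies widely between people: the SD is 114.19/258.25 = 44% of the mean. To the extent that strong participants at baseline are still strong at week 13, part of that spread is predictable and could be removed from the error term. Neither the allocation nor the analysis, as described, limits the influence of a chance difference in baseline strength.

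Sections 2.1 and 2.8 also leave the analysed variable unclear. One speaks of improvement, the other of outcomes, and the sizing uses the SD of a level. A baseline-adjusted model removes this ambiguity, because its treatment coefficient is the same whether the dependent variable is the week-13 value or the change from baseline.

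**Working it through.** **Inputs from the protocol.** Mean 258.25 N, SD 114.19 N, difference 20%, 90% power, 101 per group before dropout and 111 after (section 2.1); two-sided 5% level (section 2.8); 1:1 allocation (section 2.3).

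**Assumed.** r, the correlation between baseline and week 13, taken as 0.3 to 0.7; equal SD at both visits.

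**1. The plan's own figure.** The target is 0.20 × 258.25 = 51.65 N, or 51.65/114.19 = 0.452 SD. For an unadjusted two-sample comparison,

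n = 2 × [114.19 × (1.960 + 1.282)/51.65]² = 102.7, so 103 per group.

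The protocol states 101, which is within 2. The sizing therefore corresponds to an unadjusted comparison of levels.

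**2. Precision if week-13 values are compared.** ANCOVA replaces the SD by SD × √(1 − r²), so the variance falls by r². The 111 randomised less 10% leave 99.9, taken as 100 per arm. The standard error (SE) of the difference is residual SD × √(2/100), and power is close to Φ(51.65/SE − 1.960).

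| r | Variance cut | Residual SD (N) | SE (N) | Power | n per group for 90% |
|---|---|---|---|---|---|
| unadjusted | 0% | 114.19 | 16.15 | 89.2% | 103 |
| 0.3 | 9% | 108.93 | 15.40 | 91.8% | 94 |
| 0.5 | 25% | 98.89 | 13.98 | 95.8% | 78 |
| 0.6 | 36% | 91.35 | 12.92 | 97.9% | 66 |
| 0.7 | 49% | 81.55 | 11.53 | 99.4% | 53 |

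**3. Chance imbalance at baseline.** With 111 randomised per arm, the SE of the baseline difference is 114.19 × √(2/111) = 15.3 N. Given a baseline difference of that size, the unadjusted week-13 estimate is expected to move by r times it:

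- r = 0.3: 4.6 N, or 9% of 51.65 N
- r = 0.5: 7.7 N, or 15%
- r = 0.7: 10.7 N, or 21%

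**4. Precision if change scores are compared.** The SD of the change is SD × √(2(1 − r)). The number per group for 90% power is then 144 at r = 0.3, 103 at 0.5, 83 at 0.6 and 62 at 0.7. The ratio of ANCOVA variance to change-score variance is (1 − r²)/(2(1 − r)) = (1 + r)/2, which never exceeds 1. Change scores do better than the unadjusted test only when 2(1 − r) < 1, that is, when r > 0.5.

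**The case against.** The strongest reply is that nothing here is an error. A two-sample t-test in a randomised 1:1 trial keeps its type I error and is unbiased on average, and the trial is sized for that test and comes close to its planned 90% power. All of this stands. A reader might infer that the comparison is biased or the trial underpowered for want of adjustment; the documents support neither. Chance imbalance is already allowed for in the t-test's standard error, and it carries into the estimate only by the factor r, not in full.

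A second reply is that covariates belong in an analysis plan that is not shown. That would be fair if the protocol were silent. It names the tests for outcomes, so the method is stated, although it never uses the word unadjusted.

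A third is that improvement in section 2.1 may mean that changes are compared. Baseline would then be used, and the gains in step 2 would not apply as they stand. At r = 0.7 most of the gain would already be had (62 per group, against 53 for ANCOVA and 103 unadjusted). Section 2.8 does not say this, however, and at r = 0.3 change scores would need 144 per group. This reading makes the figures conditional but does not remove the advantage of ANCOVA.

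Finally, a reader might infer that the option of a non-parametric test means a different hypothesis will be tested. That goes too far: under a pure location shift a rank test addresses the same null. It remains true that a rank test alone does not report the mean difference on which the trial is sized.

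**Conclusion.** The point holds as a free improvement, not as the correction of an invalid analysis. The protocol states a valid but less efficient comparison while collecting the covariate that would sharpen it.

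If week-13 values are compared, the gain in power at about 100 per arm runs from under 3 percentage points at r = 0.3 to about 10 at r = 0.7. Adjustment also removes the expected shift from a chance baseline difference. If changes are compared, the gain over the plan is smaller at high r and larger at low r, and ANCOVA is never the less precise choice.

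The direction of the conclusion does not depend on r, but its size does. The protocol gives no value for r and no evidence on how much of the spread persists from baseline. The figures apply to lumbar flexion strength, the only outcome for which the protocol gives an SD.

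**What to change.** Amend section 2.8 so that each continuous primary and secondary outcome is analysed by ANCOVA of the week-13 value, and likewise the week-25 value, on arm and the baseline value of the same measure. A mixed model over both visits with baseline as covariate is an alternative. It is similar to separate ANCOVAs but not identical when visits are missing, since it also uses participants seen at only one of the two.

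Report the adjusted mean difference with its 95% confidence interval, and keep the rank test as a sensitivity analysis. Sex may be added as a covariate; this is optional. State in section 2.1 that improvement means the baseline-adjusted difference at week 13.

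The cost is a change of wording. The sample size can stay as it is.

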2.3 Randomization, allocation concealment and blinding

The random allocation sequence will be produced by an independent statistician using the statistical software SAS9.1. The participants will be allocated to either Baduanjin exercise or usual exercise control group according to 1:1 equal proportion rule. The random allocation sequence will be managed by a specified project manager who is not involved in the recruitment program.

The random allocation sequence will be managed by the project manager. The project manager and exercise coaches will be not involved in the assessment of outcome; and the outcome assessors and the statistic analyzer will be not involved in the participants’ screening and allocating.

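### Section 2.8 plans a sex-stratified subgroup analysis but names no arm-by-sex interaction test; read naturally, it gives within-sex P values that cannot show whether the effect differs by sex

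*Protocol*

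**What the plan says.** Protocol Section 2.8 gives the subgroup plan in one sentence: "Subgroup analysis stratified by participants’ sex will be used for the primary outcomes". For continuous outcomes the same section names a t-test or a non-parametric alternative, and for categorical ones a chi-squared or Fisher test. One threshold covers everything: "The statistical significance is defined as two-sided P value of <0.05". No regression model, interaction test or rule for interpreting subgroup results appears. Section 2.6.1 lists six primary outcome entries, one of which (lumbar muscle strength) has four components.

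Section 2.1 sizes the trial on the whole sample, for lumbar flexion strength only. The pilot mean and SD for "the lumbar flexion muscle strength was 258.25 newton (N) and 114.19 N respectively", and the target is given as "To detect a 20% mean difference on the Baduanjin exercise at the end of intervention", "with a type I error of 5% (α= 0.05) and 90% power (β= 0.10". No sex split is given for the trial or for the 20 pilot participants.

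**The concern.** A subgroup analysis by sex is meant to show whether the intervention works differently in men and women. A P value below 0.05 in one sex and above it in the other does not show that. The two results can differ by chance, or because one sex has fewer participants, while the underlying effects are the same. The direct test is the difference between the two within-sex effects, which is the arm-by-sex interaction.

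The trial was powered for the full sample, so each sex on its own has clearly less than the planned 90% power. That is the setting in which significance in one sex only turns up easily without any real sex difference. At stake is a claim that Baduanjin helps one sex and not the other, or a positive result in one sex being used to offset a null overall result. Section 2.8 plans neither use, but it has no rule against them.

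**Working it through.** **Inputs from Section 2.1.** Mean 258.25 N; SD 114.19 N; difference 20% × 258.25 = 51.65 N, or 51.65/114.19 = 0.452 SD; two-sided α = 0.05 (sidedness from Section 2.8); power 90%; 101 per group before dropout.

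**The plan's own figure.** n per group = 2 × [114.19 × (1.960 + 1.282)/51.65]² = 102.7, so 103. The protocol says "101 participants per group are calculated according to the formula". That is within 2 participants, and 101 per group has power 0.895. The planning inputs are therefore understood correctly.

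**Assumptions not in the protocol.** An even sex split, rounded to 50 per arm per sex; the same true effect of 51.65 N in both sexes; SD within each sex equal to 114.19 N.

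**Power within each sex.** A two-sided t-test at 0.05 with 50 per arm and d = 0.452 has power p = 0.610.

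**Significance in exactly one sex.** The two sexes are independent samples, so the probability is p₁(1 − p₂) + p₂(1 − p₁) = 2 × 0.610 × 0.390 = 0.476. Both significant: 0.372. Neither: 0.152. A simulation of 50,000 trials gave 47.8% for exactly one sex.

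**Interaction test on the same trials.** The effects are equal, so every significant interaction is a false signal. The rate is 5% by design, and the simulation gave 4.9%.

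**Sensitivity of the 48%.** One assumption is changed at a time.

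| Change | Power in each sex | Significant in exactly one sex |
|---|---|---|
| None | 0.61 | 0.48 |
| True effect × 0.5 | 0.20 | 0.32 |
| True effect × 0.75 | 0.39 | 0.48 |
| True effect × 1.25 | 0.80 | 0.32 |
| True effect × 1.5 | 0.92 | 0.15 |
| Within-sex SD × 0.9 | 0.70 | 0.42 |
| Within-sex SD × 0.8 | 0.80 | 0.32 |
| Within-sex SD × 0.6 | 0.96 | 0.07 |
| Split 25/75 (25 and 75 per arm) | 0.35 and 0.79 | 0.59 |

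For the 25/75 split: 0.347 × 0.214 + 0.786 × 0.653 = 0.587.

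**Power of the interaction test.** With 50 per arm per sex, the standard error of the difference between the two within-sex effects is 114.19 × √(4/50) = 32.3 N. For a between-sex difference of 51.65 N, power is Φ(51.65/32.3 − 1.96) = Φ(−0.36) = 0.36. The difference detectable with 80% power is (1.96 + 0.84) × 32.3, about 90 N. Neither figure takes credit for baseline adjustment.

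**Other primary outcomes.** The protocol gives no effect size or SD for them, so none of these figures can be computed there.

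**The case against.** The strongest objection is that the protocol never says in words that the tests are repeated within each sex. It does not exclude an interaction test, and it does not say that a within-sex P value counts as evidence of efficacy. Interaction terms and rules for reading subgroups are often left to a statistical analysis plan, and one may exist here. The plan is also restrained: one factor, fixed in advance, limited to the primary outcomes, with no sex-specific hypothesis.

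Part of this stands. A reader might infer that the protocol chose separate tests in place of an interaction test. The text does not support that; separate testing is the natural reading, not a stated choice. What remains is that Section 2.8 fixes a stratified method, names only two-group tests and sets one threshold. Followed as written, it does not produce a test of effect modification.

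A reader might also infer that about half of all such trials would mislead, on any primary outcome. The documents do not support that either. The figure applies to lumbar flexion at the design effect, and the within-sex SD matters most. If part of the pilot SD of 114.19 N comes from a strength difference between men and women, the SD within each sex is smaller and the figure falls.

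Nor do the within-sex tests double the chances of a positive result. They add two tests to one overall test, and multiplicity across the primary outcomes is a separate matter.

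**Conclusion.** The point holds as a cheap improvement to the analysis, not as an error in a stated figure. That within-sex P values cannot answer whether the effect differs by sex depends on none of the numbers. The numbers show how often the approach could mislead. For lumbar flexion strength, about 48% of trials with identical effects would be significant in one sex only, against about 5% false signals from an interaction test. This rests on three assumptions: the 20% effect in both sexes, a within-sex SD equal to the pilot SD, and an even sex split. Over the alternatives examined the figure runs from about 7% to about 59%.

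**What to change.** Add to Section 2.8 wording such as: for each primary outcome, effect modification by sex is assessed by an arm-by-sex interaction term in a linear model containing arm, sex and the baseline value of that outcome; within-sex effects are reported as estimates with 95% confidence intervals; the analysis is exploratory, and no claim of efficacy in one sex is based on within-sex P values.

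Section 2.8 has no such model at present, so it must be added, not just referred to. The baseline values are already collected under Section 2.6. The cost is one extra model per primary outcome, with no change to recruitment, assessments or intervention. The drawback is the interaction test's low power, about 36% for a 51.65 N difference between the sexes. A non-significant interaction should therefore not be read as proof that the effect is the same in men and women, which is a further reason to call the analysis exploratory.

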2.6.1 Primary outcomes

• Lumbar muscle strength consists of flexion, extension, lateroflexion, and rotation myodynamia. It will be assessed with the *Tergumed Work Station* (produced by Proxomed GmbH, Germany; product type: Flexion Work Station:Tergumed Flexion; Lateral Flexion Work Station: Tergumed lateral Flexion; Extension Work Station: Tergumed Extension; Rotation Work Station: Tergumed Rotation) by experienced operators at the Evaluation Department of Rehabilitation Hospital Affiliated to FJTCM.

• Lumbar proprioception function will be measured by the *Prokin* proprioception evaluation and training system (produced by Tecnobody .S.r.l, Italy; product type: PK254P) by the Evaluation Department of Rehabilitation Hospital Affiliated to FJTCM.

• The Symptom Checklist-90 (SCL-90) will be used to measure self-reported symptom intensity.

• Stress will be measured with the Chinese Perceived Stress Scale (CPSS).

• Self-efficacy will be assessed with General Self-efficacy Scale (GSES).

• Attention will be assessed by Schulte Grid (8*8) test.

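### The stated 5% error and 90% power cover one comparison, flexion strength at end of intervention, but six unranked primary outcomes (at least nine measures, two visits) share the same 0.05 threshold

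*Protocol*

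**What the plan says.** Protocol Section 2.6.1 places six items under primary outcomes, with no order among them: lumbar muscle strength, lumbar proprioception, SCL-90, CPSS, GSES and the Schulte grid. The first item has four parts: "Lumbar muscle strength consists of flexion, extension, lateroflexion, and rotation myodynamia".

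On timing, Section 2.6 says "All primary and secondary outcomes will be assessed at baseline, 13 weeks (end of intervention), and 25 weeks (after the 12-week follow-up period". It does not single out either post-baseline visit.

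On analysis, Section 2.8 says "Baseline characteristics and outcomes between groups will compare using the t-test or non-parametric test for continuous variables", adds a subgroup analysis by sex for the primary outcomes, and closes with "The statistical significance is defined as two-sided P value of <0.05".

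On sizing, Section 2.1 says "We use the improvement of lumbar flexion muscle strength as the main effect indicators to estimate the sample size". The target is set as "To detect a 20% mean difference on the Baduanjin exercise at the end of intervention", and the result is "101 participants per group are calculated according to the formula with a type I error of 5% (α= 0.05) and 90% power (β= 0.10".

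**The concern.** The sample size treats one measure at one visit as the comparison that matters and gives it all of the 5% error. The outcome section gives primary status to at least eight further measures, and the analysis section applies the same 0.05 to each. Nothing in the protocol links the two: flexion has no special standing in Section 2.6.1, and no order, adjustment or success rule says how the primary results combine.

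Two things are at stake. If a single significant primary result is enough, the trial's false positive risk is well above the 5% in Section 2.1. The headline result could also be chosen after the data are seen.

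**Working it through.** **Inputs.** From Section 2.1: mean 258.25 N, SD 114.19 N, difference 20%, alpha 0.05, power 90%, dropout 10%. From Section 2.6.1: six outcomes. Four strength directions plus one measure for each of the other five give 4 + 5 = 9, a minimum. From Section 2.6: two post-baseline visits. From Section 2.8: two-sided 0.05. The documents give no correlations, so those below are assumptions.

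**1. Reproduce the plan's figure.** Difference = 0.20 × 258.25 = 51.65 N. Standardised difference = 51.65 / 114.19 = 0.452.

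n per group = 2 × [(1.960 + 1.282) × 114.19 / 51.65]² = 102.7, so 103, against 101 stated. Power at 101 is 89.5%. A one-sided test would need only 84, so the stated figure is a two-sided calculation. For dropout, 101 × 1.1 = 111.1 gives the stated 111. The figure therefore reproduces closely as a single test at the full 0.05, with no error reserved for any other primary outcome.

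**2. Chance of at least one false positive, if any one significant result counts.** For k independent tests this is 1 − 0.95^k. The correlated values come from simulating 200,000 sets of equally correlated normal test statistics with no treatment effect.

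| Tests | Independent | Correlation 0.5 | Correlation 0.9 |
|---|---|---|---|
| 6 (outcomes, one visit) | 26.5% | 20.8% | 11.0% |
| 9 (measures, one visit) | 37.0% | 26.8% | 12.4% |
| 12 (6 × 2 visits) | 46.0% | 32.0% | 13.5% |
| 18 (9 × 2 visits) | 60.3% | 39.8% | 15.0% |

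For 18 tests with correlation 0.5 between outcomes and 0.6 between visits, the figure is 42.7%. With a mixed structure (0.1-0.5 between outcomes, 0.7-0.85 among strength directions, 0.6-0.8 between visits), it is about 24-32% for nine tests and 35-50% for eighteen. The sex subgroup tests are not counted.

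**3. If all listed outcomes had to be significant.** Type I error is then not inflated, but power is no longer 90%. As an illustration, if each of six independent outcomes had 90% power, the chance that all succeed is 0.90^6 = 53%. The protocol gives no effect size for the other five.

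**4. If an adjustment were simply added.** With Bonferroni, flexion would have this power at 101 per group:

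| Tests | Alpha per test | Power at 101 | n per group for 90% (with 10% dropout) |
|---|---|---|---|
| 6 | 0.0083 | 71.8% | 151 (168) |
| 9 | 0.0056 | 67.1% | 161 (179) |
| 18 | 0.0028 | 58.8% | 179 (199) |

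A flat adjustment over the listed primaries therefore cannot keep the stated 90% at the planned size.

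**The case against.** The strongest reply is that Section 2.8 is short and generic. It sets a threshold; it does not say that multiplicity will be ignored or that one significant result makes the trial positive. Hierarchy and adjustment are often left to an SAP, and one may exist. This stands in part: silence on adjustment is not itself an error here. But the list of primary outcomes, the sized comparison and the threshold are all fixed in the protocol. An SAP could reconcile them only by narrowing the primary list or by giving up the stated power (step 4).

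Three stronger readings are tempting, and the documents do not support them.

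- A reader might infer that the protocol contradicts itself on what is primary. It does not. Flexion strength is a component of the first listed primary outcome, and sizing on one of several primaries is a mismatch, not a contradiction. Section 2.1 can even be read as marking flexion at 13 weeks as the lead endpoint; Sections 2.6.1 and 2.8 do not carry that through.
- A reader might infer that the false positive risk simply is 37% or 60%. Both figures need independence, which is implausible for four directions of lumbar strength or one scale measured twice, and both need an any-one-wins rule that the protocol never states.
- A reader might infer that 25 weeks is a second primary time point. Section 2.6 is a visit schedule for primary and secondary outcomes alike, and Section 2.1 ties the sized comparison to the end of intervention. The eighteen-test count is therefore the widest reading. The sex subgroup analysis is not a primary test either.

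The possible bias in self-reported scales when participants know their arm is a separate matter and plays no part in this point.

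**Conclusion.** The point holds in this form: the stated 5% error and 90% power describe flexion strength at the end of intervention, not the primary family that Section 2.6.1 lists and Section 2.8 tests at 0.05.

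The size of the inflation depends on two things the protocol does not give, the success rule and the correlations. Under any-one-wins, the chance of a false positive runs from about 11% (six tests, correlation 0.9) to about 60% (eighteen independent tests). Independence is not a strict upper limit, but every scenario computed is more than double 5%, so the conclusion does not depend on the count of nine or on independence. Under an all-must-succeed rule error is not inflated, and the fault moves to the power statement. On either rule, Sections 2.1, 2.6.1 and 2.8 do not describe the same primary test.

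**What to change.** Amend the protocol before any outcome data are seen.

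1. Name lumbar flexion strength at 13 weeks, the outcome already sized on, as the primary test at two-sided 0.05.
2. Only if it is significant, test the other listed primary measures at 13 weeks with Holm: the three other strength directions, proprioception, SCL-90, CPSS, GSES and the Schulte grid. With one score each, that is 3 + 5 = 8 tests, and the smallest p-value is compared with 0.05 / 8 = 0.00625. The gate matters: an ungated Holm family beside a 0.05 primary test could give up to about 10% overall error, whereas the gated order keeps it at 5%.
3. Report the 25-week results, the sex subgroups and the Section 2.6.2 outcomes as estimates with confidence intervals, without confirmatory claims.

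Sample size and data collection do not change. The real cost falls on the psychological outcomes. Section 1 gives physical and mental health equal place in the aim. Mental health stays in the confirmatory family, but a psychological claim would need flexion to succeed first and would face a stricter threshold.

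The sponsor may prefer one physical and one psychological co-primary with split alpha. The power statement would then have to be restated. With an even split, flexion at 101 per group has expected z = 0.452 × √(101 / 2) = 3.21. Against the critical value 2.24 for alpha 0.025, that gives power of about 83%. The psychological outcome would need its own sizing assumptions.
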